### Control group and contamination

Childcare centres allocated to the control group will receive usual care during the intervention period. Usual care includes general support from health promotion officer upon request to implement the state-wide obesity prevention program [27]. Support provided to centres within the HNE region to implement this state-wide program is centrally monitored by the research team. Enhanced support to implement the healthy eating practices targeted in the intervention will be offered to control centres after 12-month follow-up data collection is complete. Assessment of potential contamination will be collected via a telephone interview with nominated supervisors and centre champions during follow-up data collection.

### Outcomes

#### Feasibility of intervention

Feasibility of the intervention, defined as the extent to which the intervention can be successfully used or carried out within the childcare setting [54] for a fully-powered implementation trial, will be assessed through childcare centre and parent recruitment and consent rates for each component of data collection.

#### Childcare centre uptake of implementation strategies

Childcare centre use of Childcare EATS will be assessed through data provided via Google Analytics [55]. These analytics include, but not limited to, total time logged into the program, completion of the self-assessment and action plan, most frequently used program features and the number of requests for assistance. The research team has previously used these metrics to evaluate childcare centre adoption of web-based programs [21, 56]. Internal records detailing the provision of implementation strategies, including the completion, duration and centre staff in attendance at the educational outreach visit; type (i.e. telephone, email, online training), frequency and duration of ongoing support; centre staff signatories on the memorandum of understanding; and selection of a centre champion, will be maintained by research team members.

#### Acceptability of implementation strategies and intervention

Supervisors and champions of the childcare centres randomised to the intervention group will complete a telephone interview to assess acceptability during follow-up data collection (6 and 12 months). Acceptability will be defined as the perception amongst centre staff that the intervention and implementation strategies are agreeable, palatable or satisfactory [54]. This will be assess using modified items by Weiner et al. [57] and items previously used by the research team to capture data on perceived intervention effectiveness, unintended consequences, reach and adoption and acceptability (workforce, infrastructure, time requirements) [46, 58] and engagement with Childcare EATS [59].

#### Appropriateness of implementation strategies

Appropriateness, defined as the perceived fit, relevance or compatibility of the intervention and implementation strategies for the childcare setting [54], will be evaluated through information collected during follow-up telephone interviews with centre supervisors and champions. The telephone interviews will include modified items by Weiner et al. [57] and items used by the research team in previous childcare interventions [33].

#### Implementation context

Relevant constructs within three of the five domains of the CFIR [60] (inner setting (compatibility with centre values and direction, level of priority). innovation characteristics (perceived complexity and cost) and outer setting (external influences such as policies, regulations and peer behaviour)) will be used to identify factors associated with implementation at follow-up during a telephone interview with childcare supervisors [17, 60].

#### Potential effectiveness of the implementation strategy in improving implementation of targeted healthy eating practices

Childcare centre implementation of the targeted healthy eating practices (e.g. provision of intentional learning experiences about healthy eating and staff professional development in nutrition) and additional data on centre nutrition environments will be assessed with the Environmental and Policy Assessment and Observation (EPAO) tool [61]. Per EPAO protocol, a trained RA will undertake a one-day observation and review of childcare centre documentation. The EPAO has been previously used by the research team in 18 childcare centres [36] and has demonstrated high inter-observer agreement. The tool is considered to be gold standard for environmental observations in the childcare setting [61]. This will be undertaken at baseline and follow-up (6 and 12 months).

#### Child dietary intake of sodium, saturated fat and added sugar in care

The nutrient output provided by weighed food record data entered into the nutrient analysis database (FoodWorks) following the process described above will be used to measure mean sodium (mg), saturated fat (g) and added sugars (g) from all foods and beverages consumed whilst in care.

#### Mean servings of fruit and vegetables packed within lunchboxes

To determine the impact of the intervention on parent provision of healthy food in lunchboxes, the mean servings of fruit and vegetables packed within children’s lunchboxes will be assessed via observation and measurement of lunchboxes and lunchbox foods and beverages following the same process described above.

#### Centre characteristics

Operational centre characteristics will be assessed at baseline during a telephone interview with nominated supervisors. Items within the telephone interview have been used previously by the research team [33], and include centre type (e.g. preschool, long day care), number of years in operation, days and hours of operation, postcode, number of children enrolled and attending, number of staff employed and the number of Aboriginal or Torres Strait Islander children enrolled at the centre.

#### Child characteristics

Child characteristics, including gender, age, Aboriginal and/or Torres Strait Islander origin, days attending care and parent level of education, will be collected from parents/guardians when providing written consent to participate in the study.

### Power calculations

As this is a pilot study, a formal sample size calculation for the primary outcome is not required [65]. However, we estimated the number of centres required as approximately 25% of the number needed for a fully-powered implementation trial. Based on consent rates from previous web-based intervention studies conducted within the ECEC setting and allowing for a childcare centre attrition rate at follow-up of 10%, it is estimated recruitment of 22 childcare centres would be sufficient to provide data to inform feasibility of undertaking the trial [21]. To assess the impact of the intervention on child diet, an approximate difference of 0.3 servings of both fruit and vegetables is considered clinically significant based on the potential reduction in risk of chronic disease [66, 67]. As such, given the 10% childcare centre attrition rate at follow up, recruitment of approximately 440 children from 22 childcare centres (20 children per centre) will enable detection of a mean difference of 0.3 servings in intake of fruit and vegetable servings, with an alpha of 0.05 and an estimated ICC of 0.1 [32], with 80% power [35, 68] and a standard deviation of 0.6 servings. Based on unpublished internal data, this number of participants will allow detection of a clinically meaningful difference of approximately 1.9 g saturated fat, 4.7 g added sugar and 155 mg sodium [69].

### Statistical analysis

The primary trial end-point will be the 6-month follow-up. Descriptive statistics will be used to describe childcare centre and child characteristics, the feasibility, uptake of implementation strategies, acceptability and appropriateness of the intervention and determinants of implementation. At the centre level, to determine the impact of the intervention on the implementation of healthy eating practices, scores of the EPAO will be compared between intervention and control centres at follow-up, adjusting for baseline, through linear regression analysis. At the child and centre levels, multiple imputations will be performed as part of a sensitivity analysis for missing follow-up data as recommended by White et al. [70]. At the child level, mixed linear regression models will be run on all secondary outcomes, where a group by time interaction will assess effectiveness of the intervention. All models will include a random effect for childcare centre to account for potential clustering effect, as well as fixed effects for prognostic variables (SES, gender) under an intention to treat framework. At the child level, subgroup analyses by centre socioeconomic status and child gender will also be undertaken to assess whether there was a differential impact of the intervention.

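### The 80% power for child diet belongs to a single follow-up comparison, but the planned test is a group-by-time interaction; adjusting for baseline would be more precise

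*Protocol article*

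**What the plan says.** The Power calculations section says that 440 children in 22 centres, or 20 in each, "will enable detection of a mean difference of 0.3 servings in intake of fruit and vegetable servings". The assumptions behind this claim are stated as "with an alpha of 0.05 and an estimated ICC of 0.1"; the target and the spread are stated as "with 80% power [35, 68] and a standard deviation of 0.6 servings". The number allows for centre loss ("given the 10% childcare centre attrition rate at follow up"). The section gives no correlation between waves and no standard deviation of change.

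The Statistical analysis section names 6 months as the primary end-point. It specifies mixed linear models for the child-level secondary outcomes, "where a group by time interaction will assess effectiveness of the intervention", with a random effect for centre. The centre-level practice score is handled differently: "scores of the EPAO will be compared between intervention and control centres at follow-up, adjusting for baseline, through linear regression analysis".

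Study design and setting describes the data collection as repeat cross-sectional. Randomisation and blinding places allocation after baseline data collection. The secondary outcomes section has lunchboxes measured at baseline, 6 and 12 months.

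**The concern.** A power statement should describe the test that will be run. A group-by-time interaction compares the arms on change since baseline, so the sampling error of the baseline means enters the contrast. In a repeat cross-sectional design the baseline means come largely or wholly from other children. The link between waves then runs mainly through the stability of the centre, and if that is weak, subtracting baseline adds noise.

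Because baseline is measured before allocation, the two arms share one expected baseline. The analysis therefore does not need to estimate a separate baseline difference between arms, and it can use baseline as a covariate instead of subtracting it in full. The article already does this for EPAO and gives no reason for handling diet differently. What is at stake is the precision of the diet effects, which the article sets as effectiveness objectives and feeds into the decision to progress.

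**Working it through.** **Inputs from the article.** Difference 0.3 servings, SD 0.6, ICC 0.1, 20 children per centre, 22 centres, 10% centre attrition (22 × 0.9 = 19.8, taken as 10 per arm), 1:1 allocation, alpha 0.05. Two-sided testing is assumed, as sidedness is not stated.

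**Assumptions not in the article.** CAC is shown over its full range from 0 to 1. Different children are taken at each wave. The interaction is the baseline to 6-month contrast with a free baseline difference between arms.

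**Reproducing the 80%.**
- Children per arm without clustering: 2 × (1.960 + 0.842)² × 0.6² / 0.3² = 62.8, so 63.
- Design effect: 1 + 19 × 0.1 = 2.9.
- 63 × 2.9 = 183 children, or 9.1 centres, so 10 per arm, and 22 in total with attrition.
- SE with 10 centres per arm: 0.6 × √(2 × 2.9 / 200) = 0.1022.
- Power: 79.3% (noncentral t, 18 df) or 83.6% (normal).

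The stated figure is therefore that of one follow-up comparison.

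**Variances of the two analyses.**
- Between-centre variance: 0.1 × 0.36 = 0.036. Within-centre variance of a mean of 20: 0.9 × 0.36 / 20 = 0.0162. Variance of a centre mean: V = 0.0522.
- Correlation of a centre's observed means between waves: r = 0.036 × CAC / 0.0522.
- Interaction: (2/10) × 2 × [0.036 × (1 − CAC) + 0.0162].
- Baseline-adjusted: (2/10) × 0.0522 × (1 − r²).
- Ratio of the two: 2 / (1 + r).

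Power is t-based, on 18 df for the interaction and 17 df for the covariate version. For the latter, the variance is multiplied by 1 + 1/16 to allow for chance baseline imbalance.

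| CAC | r | Interaction variance | Adjusted variance | Ratio | Interaction power | Adjusted power |
|---|---|---|---|---|---|---|
| 1 | 0.690 | 0.00648 | 0.00547 | 1.18 | 94.1% | 95.9% |
| 0.8 | 0.552 | 0.00936 | 0.00726 | 1.29 | 83.4% | 89.6% |
| 0.7 | 0.483 | 0.01080 | 0.00801 | 1.35 | 77.9% | 86.5% |
| 0.5 | 0.345 | 0.01368 | 0.00920 | 1.49 | 68.0% | 81.6% |
| 0 | 0 | 0.02088 | 0.01044 | 2.00 | 50.2% | 76.6% |

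The variance columns leave out the imbalance factor. With it, the adjusted analysis still has the lower variance at every CAC: at CAC 1, the least favourable case, the ratio is 1.184 / 1.0625 = 1.11.

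**Thresholds.**
- The interaction has the same variance as the single comparison when r = 0.5, that is at CAC = 0.0522 / (2 × 0.036) = 0.725.
- It reaches 80% power from a CAC of about 0.74 (t) or 0.65 (normal). If all 22 centres are kept, the t-based threshold is about 0.66.
- The adjusted analysis reaches 80% from a CAC of about 0.4 (79.7% at 0.4).

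Simulation of centre means (40,000 runs per setting, 10 per arm) gave 94.1%, 83.5%, 68.2% and 49.7% for the interaction at CAC 1, 0.8, 0.5 and 0. For the adjusted analysis it gave 95.8%, 89.7%, 81.8% and 76.5%.

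**The case against.** The strongest reply is that the model as written has only a random effect for centre. That implies CAC 1, where the interaction has about 94% power, more than the article claims. This stands, and it rules out the tempting inference that the trial is underpowered for diet: every figure below 80% depends on a CAC that the article does not state. It does not show that centre means are in fact that stable. If they are not, a model without a centre-by-time term understates the standard error, so the 94% could not be relied on either.

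Children may also overlap between waves, since nothing excludes earlier participants. If overlap times within-child correlation were 0.2, 0.3 or 0.5 (assumed values), the 80% threshold would fall to a CAC of 0.65, 0.60 or 0.51. Zero overlap is thus the least favourable case for the interaction.

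The phrase group by time also does not say whether a baseline arm effect is fitted. A model with baseline means constrained equal is itself tested through arm-by-wave terms, and such detail may sit in an analysis plan that is not shown. If that is the intention, only the wording needs changing.

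Finally, diet is a secondary outcome in a pilot whose primary objective is feasibility, and progression has no significance threshold on diet. This limits the weight of the point. It does not affect the gain in precision.

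**Conclusion.** The point holds in a conditional form. The 80% describes a single 6-month comparison, not the planned interaction. The interaction's power runs from 50% to 94% over the possible range of CAC, and 80% is not assured below about 0.74, or lower still if children overlap or all centres are retained.

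The part that does not depend on the unknown CAC is the comparison of methods. The interaction's variance exceeds that of the baseline-adjusted contrast by 18% at CAC 1, 49% at 0.5 and 100% at 0, assuming different children at each wave and a free baseline arm effect.

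A reader might also infer that adjustment guarantees 80% whatever the CAC. It does so on the usual normal approximation (at least 83.6%). On the t-based scale with 20 centres it gives 77% to 80% for a CAC below about 0.4, because the unadjusted comparison itself starts at 79.3%. The interaction gives 50% to 64% there. The interaction test is valid; the criticism is of its efficiency and of a power statement that does not match it. The change is worth making because it costs so little.

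**What to change.** In the Statistical analysis section, define the test for each child diet outcome as the 6-month difference between arms adjusted for baseline. Either form will do:

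- a mixed model of all waves with time and arm-by-follow-up-wave terms and no arm effect at baseline; or
- a model of the 6-month data with the centre's baseline mean as covariate.

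Report the 12-month contrast separately. In the Power calculations section, state that the 80% refers to the 6-month follow-up comparison.

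No new data are needed. The covariate version costs one degree of freedom and a small loss from chance baseline imbalance (about 6% in variance with 20 centres), both already included in the adjusted power figures.

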#### Children

In order for children to be eligible to participate, they must (1) have prior written consent from a parent or guardian, (2) be between the ages of 2 and 5 years and (3) not have a dietary restriction that requires specialised tailoring of their diet (e.g. allergies, intellectual or physical disability).

Approximately 2 weeks prior to data collection, centres will be asked to distribute parent information statements and consent forms via electronic methods, including email and parent communication apps, and child pigeonholes as part of standard communication with parents. The dates of the scheduled site visits will not be disclosed to parents to avoid any changes to parent usual lunchbox packing. Additionally, approximately 1 week prior to the scheduled site visit, and on the day of the scheduled site visits, two RAs trained in recruitment and data collection procedures will be present at the childcare centre to request written consent from parents for child participation in the study.

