### Randomisation and blinding

Childcare centres will be randomly allocated following a block randomisation procedure in a 1:1 ratio to either intervention or control using a computerised random number function in Microsoft Excel 2013. Due to the demographic and socioeconomic diversity of the HNE region, randomisation will be stratified by centres with a high number of Aboriginal child enrolments (> 10%) and by centre socioeconomic status (SES), as determined by Socio-Economic Indexes for Areas categorisation using centre postcodes [35, 36]. Randomisation will be completed following baseline data collection by a statistician not otherwise involved in the trial. Staff at participating childcare centres and those delivering the intervention will be aware of group allocation. Every effort will be made to keep data collectors and analysts blind to group allocation. However, there is potential for data collectors to become aware of group allocation due to the nature of the intervention (e.g. display of intervention resources within the centre).

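### Aboriginal enrolment is a randomisation stratum but enters no model; the cost is some lost precision, mainly in the EPAO regression, and not bias

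*Protocol article*

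**What the plan says.** The protocol article's Randomisation and blinding section allocates centres by a "block randomisation procedure in a 1:1 ratio to either intervention or control". It states that "randomisation will be stratified by centres with a high number of Aboriginal child enrolments (> 10%) and by centre socioeconomic status (SES"), with SES "as determined by Socio-Economic Indexes for Areas categorisation using centre postcodes". The reason given is the region's demographic and socioeconomic diversity.

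The Statistical analysis section has two parts that matter here.
- **Centre level:** EPAO scores at follow-up are compared between arms by linear regression, adjusted for baseline.
- **Child level:** mixed linear models test a group-by-time interaction. The section then says "All models will include a random effect for childcare centre to account for potential clustering effect". The covariates are named at the end of that sentence: "as well as fixed effects for prognostic variables (SES, gender) under an intention to treat framework".

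Both candidate covariates will be available. The baseline centre interview records "the number of Aboriginal or Torres Strait Islander children enrolled at the centre". The consent form collects "Child characteristics, including gender, age, Aboriginal and/or Torres Strait Islander origin, days attending care and parent level of education". Eligible children must "be between the ages of 2 and 5 years", and data collection is repeat cross-sectional.

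**The concern.** The design treats two centre characteristics as important enough to balance, and the analysis keeps one of them. Gender, which is not a stratifier, is added; Aboriginal enrolment is dropped without explanation. The article names the covariates, so this is a mismatch between two stated parts of the plan and not a detail left for later.

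Stratifying on a factor removes its variation from the arm comparison. If the factor is then left out of the model, its variation stays in the residual, and the estimated standard error exceeds the true sampling error. With about 20 centres analysed, that could matter wherever the comparison is made between centres.

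Age is a separate and weaker point. The dietary outcomes are absolute amounts (servings, mg, g) in children aged 2 to 5. Each wave is a new cross-section, so a child's own baseline cannot absorb age.

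**Working it through.** **1. Which models contain the stratum.** The sentence on covariates speaks of all models. A centre random effect cannot be fitted to a regression with one EPAO score per centre, and gender is a child variable, so the sentence most naturally covers the child models only. The EPAO regression then adjusts for baseline alone. On the wider reading it also gains SES. Aboriginal enrolment is absent on either reading.

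**2. The plan's sample size (Power calculations section).** Inputs: difference 0.3, SD 0.6, ICC 0.1, 20 children per centre, alpha 0.05 (two-sided assumed), power 80%, centre attrition 10%.
- Individually randomised: 63 children per arm.
- Design effect: 1 + 19 × 0.1 = 2.9, so 63 × 2.9 = 182.7 per arm, or 9.1 centres, rounded up to 10 per arm.
- Attrition: 20 / 0.9 = 22.2, against the stated 22.

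The figure reproduces, and nothing below changes it.

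**3. Child-level group-by-time test.** Write the mean for centre j at wave t as

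ȳ_jt = μ + τt + αG_j + βG_j·t + γA_j + u_j + e_jt,

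with G the arm, A the enrolment stratum and u the centre effect. The change is

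ȳ_j1 − ȳ_j0 = τ + βG_j + (e_j1 − e_j0).

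Both γA_j and u_j drop out. With variance 0.6² = 0.36, the between-centre part is 0.036 and the within-centre part 0.324. The variance of the contrast is 2 × (2 × 0.324 / 20) / 10 = 0.00648 (SE 0.080), with no between-centre term for the stratum to reduce.

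Cancellation is exact for equal centre sizes. For unequal sizes it was checked with 20 centres, 12 to 27 children per centre per wave and 40% of centres in the high-enrolment stratum. The ratio of the interaction standard error with the stratum to that without it was 0.999 to 0.9997 if the stratum explains 20% of between-centre variance, and 0.998 to 0.999 at 50%.

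**4. Direction of the effect in a between-centre comparison.** A simulation of 20 centre means, with stratified 1:1 allocation and SES in both models, gave:

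| Share of between-centre variance explained (assumption) | Type I error, stratum omitted | Type I error, stratum included |
|---|---|---|
| 0% | 0.050 | 0.051 |
| 10% | 0.041 | 0.049 |
| 25% | 0.031 | 0.051 |
| 50% | 0.015 | 0.053 |

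Omission makes such a test conservative and never liberal. The simulation uses the child-diet ICC and cluster size, so it shows direction and does not size the EPAO effect.

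**5. EPAO regression.** With 20 centres and terms for intercept, arm and baseline, 20 − 3 = 17 degrees of freedom remain. Adding enrolment and a two-level SES term (assumption; the number of SES categories is not stated) leaves 15. The critical value rises from 2.110 to 2.131, a ratio of 1.010. If the strata explain nothing, the interval is about 1% wider. If they explain a share f of the EPAO variance left after baseline, the width is multiplied by about √(1 − f) × 1.010: 0.96, 0.90 and 0.85 for f = 10%, 20% and 30%. These shares are assumptions; the protocol gives no EPAO variance and no relation to enrolment.

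**6. Age.** If age has within-centre correlation r with intake, adjustment multiplies the child-level residual SD by √(1 − r²): 0.995, 0.980 and 0.954 for r = 0.1, 0.2 and 0.3. The values of r are assumptions; none is given.

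**The case against.** The strongest reply is that the omission hardly touches the outcomes where precision is usually argued over. The dietary test is a within-centre contrast, and step 3 shows that the stratum is irrelevant to it. That stands, and it confines the precision argument to the EPAO regression. There, baseline EPAO may already carry much of any stable difference between strata. That also stands, and it is why no size can be given.

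A reader might infer that adjustment would raise power from 79% to 85%. The arithmetic is right on its own terms: with 10 centres per arm and an effect of 0.5 SD, a per-centre variance of 0.1 + 0.9/20 = 0.145 gives 79% (18 df). If the stratum explains 20% of between-centre variance, 0.08 + 0.045 = 0.125 gives 85% (17 df). But this describes a follow-up-only comparison of child intake, which the protocol does not plan. Its inputs do not carry over to EPAO either, which is one score per centre with no stated ICC or target effect.

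A reader might also infer bias or a misleadingly small p-value. Randomisation protects the estimate, and the error runs in the conservative direction.

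On age, it is fair to say that omitting a non-stratifier contradicts nothing, that age will be described among the child characteristics, and that the protocol reports no age–intake relation. The suggestion is one of efficiency only. Finally, this is a pilot in which feasibility is primary, and progression is a majority judgement, not a significance test. That lowers the stakes but does not explain why one stratum is modelled and the other is not.

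**Conclusion.** The mismatch is real: centres are randomised by two factors and the models contain at most one of them. Its consequence is modest. The EPAO follow-up comparison may be somewhat conservative and less precise than the design allows, by an amount that depends on how far Aboriginal enrolment predicts EPAO beyond baseline and SES, which the protocol does not report. The child-level interaction is practically unaffected, given a random centre intercept and a stratum effect that is constant over time. Leaving age out allows chance differences in age mix between arms and waves to add noise to that interaction, also by an unquantified amount. Neither omission biases the estimates or inflates type I error. It is worth correcting because the correction is nearly free, not because the conclusions are in danger.

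**What to change.** - **EPAO regression:** state that it includes both randomisation strata (Aboriginal enrolment >10% yes/no, and SES in the categories used for randomisation) as fixed effects alongside baseline EPAO.
- **Child-level models:** add the enrolment stratum beside SES, for consistency with the design and not for a power gain. Add child age beside gender.
- If the enrolment stratum is left out on purpose, give the reason.

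The cost is wording, settled before unblinded analysis, and one or two centre-level degrees of freedom in the EPAO model (more if SES has more than two categories). No new data are needed, and the sample size does not change.
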